### Plans for collection, laboratory evaluation and storage of biological specimens for genetic or molecular analysis in this trial/future use

There are no plans to conduct genetic or molecular analysis on biological samples collected from participants enrolled in this study.

Participants have the option to consent to the use of their biological samples for future research. Future research undertaken on these samples will undergo relevant reviews by the responsible national ethics committees and/or institutional review boards before any further analyses are undertaken.

### Plans to promote participant retention and complete follow-up

The study has a flexible approach to data collection and sampling to reduce the research burden on both participants and staff who are working in the context of an outbreak.

Table 1 describes the flexibility in the days on which samples and assessments can be undertaken.

Equally, samples should only be collected where it is feasible to do so and priority samples are identified in the
*Data collection methods* section above.

Research staff at participating sites are asked to make every reasonable effort to follow participants throughout the entire study period.

### Early discontinuation and withdrawal of participants

Throughout the duration of the study, participants have the option to withdraw prematurely for various reasons, including but not limited to:

If a presumptive case enrolled in the study tests negative for MPXV, they are withdrawn.Participants may perceive certain adverse events (AE) as intolerable, leading to their withdrawal.Inability to adhere to the study procedures can also be a reason for withdrawal.Participants have the autonomy to decide to withdraw from the study.In some cases, the clinician may make the decision to withdraw a participant.

The study design provides participants with three withdrawal options, which are as follows:

1/ Participants can choose to withdraw from active follow-up and further communication. However, they allow their direct care team, acting on behalf of the study, to continue accessing their medical records and relevant hospital data that is routinely recorded as part of standard care. This data is essential for data collection on the electronic case report form (eCRF).

2/ Participants have the choice to withdraw from the study while permitting the retention of data and samples obtained up until the point of withdrawal. These retained data and samples will be used for analysis in the study, but no additional data or samples will be collected after the withdrawal.

3/ Participants may opt to completely withdraw from the study, including the request to remove the data and samples collected up until the point of withdrawal. In this case, the data and samples already obtained will not be utilized in the final study analysis.

The eCRF records both the type of withdrawal and the reason for withdrawal, ensuring proper documentation and tracking of participant decisions and the underlying motivations for their withdrawal from the study.

### Expenses and benefits

There is no cost to participants and no payment is made for participation in the study. Participants are reimbursed for incidental expenses related to enrolment according to local approvals and practice.

### Definition of end of study

End of study is defined as the date of the last visit (D180 or date pregnancy outcome is known) of the last participant enrolled in the study or the date that all samples have been analysed, whichever is later.

There are jurisdictional differences in reporting end of study data. In the EU, a summary of study results will be submitted within one year of the last participant visit and will not be postponed for secondary sample analysis. This information will be provided without delay when they are available.

## Data management

### Source data

Source documents serve as the initial records of data and are used to obtain participants' data for the electronic case report form (eCRF). These source documents encompass a variety of materials such as hospital records (including medical history and medication details summarized into the eCRF), clinical and office charts, laboratory and pharmacy records, diaries, microfiches, radiographs, and correspondence. If the eCRF is the sole place where data is originally recorded without any other written or electronic records, the entries in the eCRF are considered source data.

In this study, primary data collection occurs through two main methods:

(i) Study staff at participating sites complete electronic case report forms on enrolment, during scheduled study visits, daily for in-patients, and whenever laboratory results become available.

(ii) Participants complete an online questionnaire daily during the first 14 days of the study (or while they are in the hospital) and at specific time points (D21, D28, D60, and D180).

The data entered in the electronic case report forms and the online questionnaire are stored in separate REDCap databases.

To ensure data quality, automatic data checks are programmed into the REDCap systems, alerting users during data entry to minimize missing, inconsistent, or erroneous data. Study sites are responsible for reviewing the data entered into the case report forms for their respective participants.

Centralized monitoring of all data collected in the study is conducted by the University of Oxford. This monitoring involves evaluating data compliance with the study protocol and assessing accuracy, as outlined in the study-specific Monitoring Plan. When issues are identified, queries are triggered to be resolved by the respective sites. If any issues are detected in the Participant Self-Assessment data, the study site is notified to communicate with the participant if necessary.

On-site monitoring may be necessary if serious or repeated non-compliance with the protocol is identified through centralized monitoring. Local or regional coordinating centers will carry out this on-site monitoring.

The REDCap database is hosted at the University of Oxford for a minimum of 25 years following completion of the study.

### Confidentiality

**
*Participant confidentiality.*
** The study complies with the UK General Data Protection Regulation (UK GDPR), Data Protection Act 2018 GDPR (EU) 2016/679 and the Personal Data Protection Act (Singapore), which require data to be de-identified as soon as it is practical to do so. The processing of the personal data of participants is minimised by making use of a unique participant study number only on all study documents and any electronic database(s). All documents are stored securely and only accessible by study staff and authorised personnel. The study staff safeguards the privacy of participants’ personal data.

All documents and samples are labelled with a pseudonymised subject ID code. Identifying information collected as a part of this protocol remains confidential.

Participants’ names, telephone numbers and email addresses are recorded by the clinical site staff at the time of consent to enable follow-up of the self-assessment questionnaire complementation and follow-up visits. Identifiable information is linked to stored data or samples only by a protected master list. This list is not shared outside the clinical site staff and no identifying information are transferred between study sites or to the study Sponsor.

All eCRF forms and samples are labelled only with a subject identification number and stored in suitable secure locations. Only persons who have undertaken the locally appropriate data protection training have access to the password-protected computer where entered data is stored.

The eCRF and the online questionnaire constitute the records held in the study main database. These will be retained for at least 25 years from the completion of the study. Identifiable data will be retained only as long as it is required. Informed consent forms will be retained securely by the recruiting sites depending on their jurisdictional requirements.

## Statistical methods

The statistical aspects of the study are summarised here with details fully described in a statistical analysis plan (SAP) currently being drawn up by the Statistical analyses group. The SAP will be finalised before any analysis takes place.

The SAP will be developed by the investigators and published whilst still blind to any analyses of aggregated data on study outcomes by treatment status. It will describe the outcomes, efficacy and safety variables and anticipated data transformations and manipulations, and other details of the analyses not provided in this study protocol.

General statistical methods are outlined hereafter.

### Statistical method

**
*Sample size.*
** This is an observational study. We are interested in the effect of any available treatment against mpox used in the cohort and thus defined treatment outcomes (see below). However, due to the observational nature of this study, there is no formal sample size calculation to assess treatment effect. The availability of treatments and prescription rules differ in time and across countries. Any causal inference analysis will account for confounding effects, pre-specified in the statistical analytical plan.

**
*Participant flowchart.*
** The total number of patients and the flowchart of the study will be presented with the number of patients excluded (with reasons for exclusion, and number of patients for each reason), included, receiving any antiviral drugs, lost-to-follow-up and analysed.

**
*Descriptive statistics.*
** Patients’ demographics and baseline characteristics will be described overall and across analysis groups (
*e.g.*, treated with and without tecovirimat), by using, for continuous variables: sample size, mean, standard deviation, median, interquartile range, minimum and maximum; and for categorical variables: sample size, proportion and number of patients in different categories.

The number of missing values, overall and per group, will be reported.

**
*Inferential statistics.*
** Causal inference methods will be used to derive information on the effects of tecovirimat (or other antiviral drugs) on patients’ outcomes (see below) and assessed from a Cox proportional hazard model. Graphics and tables associated to the analysis of each outcome will be fully detailed in the SAP.

**
*Primary outcome.*
** The time to lesion resolution will be summarized for the overall population and stratified by treatment status using Kaplan-Meier curves, median time-to-event, proportion of resolution at D14, and associated 95% confidence intervals (CIs).

**
*Secondary outcomes.*
** For clinical status at D14 and D28, counts and percentages will be presented with their associated 95% CI. The four-point ordinal scale will be used to estimate a proportional odds model. Recrudescence or relapse will be compared between treatment status with a logistic regression model.

Regarding virologic endpoints, the analysis will present the medians and interquartile ranges of mpox virus levels, measured in Cycle threshold (Ct) values, at different time points including baseline, and on days 4, 8, 14, and 28. These measurements will be used to assess viral clearance, categorized as a binary variable, in blood, skin lesions, and throat. The frequency of viral clearance will be reported based on the day of follow-up and treatment status groups.

Additionally, change in mpox virus DNA levels in throat and blood swabs will be compared to baseline on days 4, 8, 14, and 28 and will compared between treatment status using linear regressions at each timepoint.

Logistic regressions will model the presence of mpox virus DNA in lesion swabs at each timepoint.

Regarding safety endpoints, the number and type of SAEs, SARS and SUSARs within 28 days of enrolment will be described.

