^d^Samples are only collected where feasible and permitted under local and national regulations on mpox infection prevention and control. Where local capacity limits sample collection, sites should prioritise the collection of D14 and D28 samples—all other samples are optional. Baseline samples are the participant’s diagnostic samples, which may have been collected for routine care before study participation commenced.

^e^An additional sample should be collected at D21 if the participant has a positive PCR on D14.

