### Participant timelime

Enrolment is the day that the informed consent form is signed, and the participant is enrolled in the study. Enrolment may be any day once the diagnostic sample is taken or after the patient has been considered a “presumptive case” by their treating clinician.

After enrolment, days are counted from the date the diagnostic sample is taken:

Day 1 is the date that the first sample to diagnose mpox was taken, regardless of when results became available. If the participant is enrolled on the same day that the diagnostic sample is taken, enrolment occurs on Day 1.If a participant is enrolled after the date that the diagnostic sample was taken, then study procedures start from the number of days since the sample was taken.

Participants who do not receive treatment follow the schedule from D1 and continue until D180. Participants who receive treatment immediately following diagnosis and enrolment in the study follow the schedule described above.

If a participant enters the study without receiving treatment and then begins receiving treatment at a later date, they initiate a new schedule of procedures by restarting at D1. This second D1 represents the date of treatment start. This extends the study participation period by the number of days between enrolment and treatment initiation.

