### Data collection methods

All data are recorded by the clinical and study teams directly on the REDCap (version 13.1.30)
^
9
^ electronic Case Report Form (eCRF) for each timepoint as defined in
Table 1.

**
*Demographics and medical history.*
** Data relating to the participant’s demographics and medical history are collected at baseline. Demographic includes sex at birth and ethnic group. Medical history includes data on comorbidities, results of pregnancy and HIV tests, data on signs and symptoms experienced by the participant between the collection of mpox diagnostic sample and the point of consent, and details of potential AEs and SAEs occurring between the collection of mpox diagnostic sample and the point of consent.

**
*Medical assessments.*
** Medical assessments are undertaken at baseline, and D14, 28, 60, and 180. These assessments can be conducted in person,
*via* video link or telephone. The data collected include the participant’s signs and symptoms, any treatment they may be receiving for mpox, AEs and SAEs details.

**
*Biologic sampling.*
** Baseline samples are the participant’s diagnostic samples that may have been collected under routine care before the participant signed the consent form. Blood* (~0.5ml to 20ml depending on local collection procedures), two lesion swabs and one throat swab are collected at D4*, 8*, 14, 21* and 28 where feasible to do so and permitted under local and national regulations–the asterisk (*) denotes procedures only for hospitalised subject; day 21 and 28 sampling only if day 14 sample is still positive.

Where local capacity limits sample collection, sites should prioritise the collection of D14 and 28 samples. All samples are tested by PCR only conducted in local laboratories in each participating country.

In Tier 2 in France, in addition to the sampling covered in Tier 1, additional samples of mucosa, saliva, anus, urine, semen or vaginal secretions, and blood are collected at baseline, D8, D14, D28, D60 (in case of oral, genital or anal lesion) and D180 (only if sample is positive at D60).

In Tier 3 in France, in addition to the sampling covered in Tier 1 and 2, additional samples of blood are collected at D28, D60 and D180.

Samples in Tier 2 and 3 are tested as in
Table 2.

**Table 2. T2:** Tests by sample type.

TIER	Test	Sample							
		Lesion	Throat	Mucosal lesion	Saliva	Anus	Blood	Urine	Semen or vagina secretion
1	PCR	X	X				X		
1&2	Bacterial STIs detection		X			X	X	X	

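### For participants treated some days after the diagnostic sample, change in viral DNA at each visit spans more days than in the comparison group, because baseline stays at diagnosis while Day 1 moves to treatment start

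*Protocol article*

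**What the plan says.** Four statements in the protocol article bear on this point.

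- **Baseline sample.** Table 1, footnote d: "Baseline samples are the participant’s diagnostic samples, which may have been collected for routine care before study participation commenced". The biologic sampling paragraph under Data collection methods agrees: "Baseline samples are the participant’s diagnostic samples that may have been collected under routine care before the participant signed the consent form". Neither makes an exception for treated participants.
- **Clock.** The Participant timeline section sets Day 1 at the date of the first diagnostic sample. A participant who enters untreated and starts treatment later restarts the schedule: "This second D1 represents the date of treatment start". Participants treated immediately after diagnosis and enrolment stay on the diagnostic clock. The abstract's Methods paragraph also allows either origin for the sampling days.
- **Sampling days.** Table 1 lists lesion swabs, throat swab and blood at Baseline and next at D4. It lists none at D1.
- **Analysis.** Under Statistical method, "change in mpox virus DNA levels in throat and blood swabs will be compared to baseline on days 4, 8, 14, and 28", and the change is "compared between treatment status using linear regressions at each timepoint". Virus level is measured in Ct. No correction for elapsed time is stated.

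**The concern.** A change from baseline can be compared between groups only if it covers the same length of time in each. Here the start of the interval (the diagnostic sample) and the origin of the visit days (treatment start) separate for anyone treated after a delay. They coincide for everyone else. The extra days fall in one group only, so whatever the virus does by itself in those days enters the treatment coefficient.

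If viral DNA is falling over that period, a drug with no effect would appear to lower it in throat and blood. These are the only quantitative virologic comparisons by treatment status in Tier 1, so a spurious signal could be read as evidence of antiviral activity.

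**Working it through.** The protocol gives no effect size, power or sample size for this endpoint, so there is no figure to reproduce. The check is interval arithmetic followed by an illustration.

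**Step 1. Days from baseline sample to visit.** Let L be the days from diagnostic sample to treatment start. Day 1 is the origin date itself, so Day d falls d − 1 days after it.

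- Untreated or immediately treated: d − 1 days.
- Treated after a delay: d − 1 + L days.

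| Visit | No delay | L = 2 (ratio) | L = 3 (ratio) | L = 4 (ratio) |
|---|---|---|---|---|
| D4 | 3 | 5 (1.67) | 6 (2.00) | 7 (2.33) |
| D8 | 7 | 9 (1.29) | 10 (1.43) | 11 (1.57) |
| D14 | 13 | 15 (1.15) | 16 (1.23) | 17 (1.31) |
| D28 | 27 | 29 (1.07) | 30 (1.11) | 31 (1.15) |

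The excess is L days at every visit. It is proportionally largest at D4 and small by D28.

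**Step 2. Spurious difference with no drug effect.** Let s be the natural rise in Ct per day (Ct rises as DNA falls) and f the share of treated participants with a delay.

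- Per delayed participant: s × L.
- In the group mean: f × s × L.

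None of s, L and f is in the documents. The values below are assumptions, with 2-fold DNA per Ct.

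- s = 0.3, L = 2: 0.3 × 2 = 0.6 Ct, and 2^0.6 is about 1.5-fold.
- s = 0.5, L = 4: 0.5 × 4 = 2 Ct, or 4-fold.
- s = 1, L = 4: 1 × 4 = 4 Ct, or 16-fold.

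With f = 0.5 the group-mean differences in Ct halve, to 0.3, 1 and 2.

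**Step 3. Could it change a conclusion?** The Discussion reports 601 cases, with 55 on tecovirimat, 7 on cidofovir and 2 on both. If these groups are exclusive, 55 + 7 + 2 = 64 are treated and 601 − 64 = 537 are not. Assume an SD of change of 5 Ct, s = 0.5, L = 3 and no drug effect, tested two-sided at 5%.

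- All sampled, f = 1: bias 1.5 Ct. SE = 5 × √(1/64 + 1/537) = 0.66. Rejection is about 62%.
- All sampled, f = 0.5: bias 0.75 Ct. Rejection is about 20%.
- About 10% sampled (6 against 54), f = 1: SE = 5 × √(1/6 + 1/54) = 2.15. Rejection is about 11%.
- About 10% sampled, f = 0.5: rejection is about 6%.

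Sparse sampling hides the bias in the test but leaves the estimate just as biased.

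**Step 4. Does adding elapsed days to each per-visit regression repair it?** No. At a nominal visit, elapsed days equal d − 1 for every participant without a delay and d − 1 + L for the rest. Apart from the visit windows (±2 days at D14 and D28), the covariate varies only through the treatment delay. The natural slope would then be learned from differences among treated participants, not from the untreated course. It has to be estimated across visits.

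**The case against.** The strongest reply is that this is a condensed article, the SAP is still being written, and confounder adjustment is promised there. That answers many complaints about detail, but not this one. The article itself fixes the baseline sample, the restart rule, the nominal-day comparison and the type of model. Unequal follow-up is a matter of how the outcome is defined, and none of the confounders given as examples (age, smallpox vaccination, extent of lesions) corrects it.

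Other parts of the reply stand. These are secondary outcomes in a study described as primarily descriptive. The text on biologic sampling marks D4 and D8 for hospitalised participants only, so numbers will be small where the relative distortion is greatest. By D28 the excess is minor. Neither the delays nor the share delayed is given.

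A reader might also infer more than the documents support:

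- **That every treated participant is shifted.** Those treated immediately keep the diagnostic clock and are not affected.
- **That the bias must favour treatment.** This needs viral DNA to be falling in throat and blood from the diagnostic sample on. The article gives no kinetics.
- **That participants who have cleared virus drop out of later regressions because a negative sample has no Ct.** The article does not say how negatives are handled, which can be left to the SAP, and it reports clearance separately as a binary outcome. The text on biologic sampling does limit D28 samples to those still positive at D14, where Table 1 does not. That is a separate question of sampling.
- **That local PCR laboratories confound the comparison.** Laboratory or country terms can be specified in the SAP.

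**Conclusion.** The point holds for participants whose treatment starts after the diagnostic sample. Their change from baseline covers L more days than that of the comparison group at every visit, and the stated regressions attribute natural change over those days to treatment. The mismatch follows from the protocol's own definitions and needs no outside figure.

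Its size does not follow from them. The range of 0.6 to 4 Ct per delayed participant rests on assumed slopes of 0.3 to 1 Ct per day and delays of 2 to 4 days, and the group difference shrinks in proportion to the share treated immediately. The direction favours treatment only if DNA is falling. This should be corrected before analysis, but it concerns secondary virologic endpoints and does not touch the primary outcome.

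**What to change.** For throat and blood, analyse both groups on actual days since the diagnostic sample. One suitable form is a single repeated-measures model across visits for each sample type, with elapsed days as the time variable and treatment as a time-dependent term that switches on at its start date. The natural course is then estimated from untreated time, and the delay no longer counts as drug effect.

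For the descriptive tables, where a treated participant has a later pre-treatment sample, take the last sample on or before treatment start as baseline. Report the elapsed days from baseline to each visit by group in every case.

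This needs wording in the SAP, which the article says is not yet final, and a matching sentence in the protocol. It needs no new samples: the study schedule already depends on the dates of diagnostic sample and treatment start. The downsides are a slightly more complex model and possibly smaller, less precise apparent effects. The change does not address confounding by the reason for starting treatment, which still needs the adjustment promised for the SAP.

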### Outcomes

**
*Primary outcome measure.*
** The primary outcome measure of this study is the participant’s time to lesion resolution without any serious complications. Lesion resolution is the first day on which all lesions are resorbed, scabbed or desquamated and mucosal ulcers healed. Lesion resolution is assessed until a maximum of 14 days since the date that the diagnostic sample is taken (for participants who do not receive mpox-specific antiviral treatment) or the day of treatment initiation (for participants who receive mpox-specific antiviral treatment).

**
*Secondary outcomes.*
** Secondary outcome measures evaluate clinical and virologic outcomes. Clinical outcomes are assessed on the basis of:

1. Clinical status on day 14 and day 28 according to a four-point ordinal scale assessed by a physician or a study nurse. The ordinal scale is a) all lesions are resolved and no serious complications, b) active lesions and no serious complications, c) serious complication and/or hospitalization due to mpox, or d) death.2. Evidence of recrudescence or relapse at day 60 and day 180.

*Note:* A "serious complication" is any complication associated with a Serious Advent Event (SAE) that is life-threatening, results in hospitalisation, prolongation of existing hospitalisation, disability, incapacity, or a congenital anomaly; or any other complication that is considered medically significant.

Virologic outcomes in Tier 1 are assessed on the basis of:

1. Change from baseline in mpox virus DNA levels in throat swabs on days 4, 8, 14 and 28.2. Change from baseline in mpox virus DNA levels in blood on days 4, 8, 14 and 28.3. Presence of mpox virus DNA in lesion swabs on days 4, 8, 14 and 28.

The study also assesses the number and type of SAEs, Suspected Adverse Reactions (SARS) and Suspected Unexpected Serious Adverse Reactions (SUSARs) within 28 days of enrolment.

Pregnancy outcomes defined as the final known health status of the mother and child are evaluated in any participants who are pregnant during the course of the study.

**
*Exploratory outcomes in Tier 2 and Tier 3.*
** Further virologic and immunological outcomes are also evaluated in France under this protocol to learn more about viral transmission, humoral and cellular immune responses. The outcome measures are as follows:

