### Recruitment

Participants are enrolled in the study before laboratory confirmation of mpox on the basis of high clinical suspicion or at any time after they receive a positive diagnosis of mpox infection by PCR. From June 2022 to December 2022, new cases were recruited prospectively from participating sites that had been activated. Then, from January 2023, as new cases were rare, patients managed before the start of the study at participating sites or patients from newly activated sites were recruited retrospectively.

Potential participants are identified and approached to participate in this study by their clinical care team at a participating site. Identification may take place using the Site Investigator’s patient register. The Site Investigator must, in all cases, confirm that the potential participant meets the eligibility criteria before proceeding further with the inclusion process. Any patient meeting the inclusion criteria can be enrolled in the study whether they are currently managed or have previously been managed as a mpox case, provided they give their informed consent to participate.

If the potential participant meets all the eligibility criteria, information about the study is provided using the participant information sheet. The participant information sheet can be given in person during a clinic visit, or in the event that the patient is currently being managed as an outpatient and has no upcoming scheduled clinical visit, the information sheet can be sent by post or email, or it can be explained by telephone
(according to the site’s locally approved practices).

The participant information sheet details no less than: the nature of the study; what it involves for the participant; the implications and constraints of the protocol; and any risks involved in taking part. It is clearly stated that the participant is free to withdraw from the study at any time for any reason without prejudice to future care, without affecting their legal rights or their care and with no obligation to give the reason for withdrawal.

The participant is permitted as much time as desired to consider the information, and given the opportunity to question the Investigator, their doctor or other independent parties to decide whether they participate in the study.

Participation is entirely voluntary.

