### Harms

**
*Safety reporting.*
** The assessment of safety outcomes—a study objective—requires adverse event reporting, serious adverse event reporting and collection of pregnancy outcomes in both treated and non-treated cohorts.

The study procedures carry minimal risk and therefore AE related to the study procedures are not anticipated.

AE and SAE data are collected in the eCRF from the date that the participant’s diagnostic sample for mpox infection was collected or the date of enrolment (whichever comes first) until D28.

*

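### The safety outcome counts SAEs for 28 days from consent, while SAEs are collected from the diagnostic sample to D28, so events before consent fall outside the outcome

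*Protocol article*

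**What the plan says.** Outcome and analysis. The Outcomes section covers SAEs, suspected adverse reactions and "Suspected Unexpected Serious Adverse Reactions (SUSARs) within 28 days of enrolment". The safety paragraph under Statistical methods repeats the anchor: "the number and type of SAEs, SARS and SUSARs within 28 days of enrolment will be described".

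Clock. Under Participant timeline, "Enrolment is the day that the informed consent form is signed, and the participant is enrolled in the study". The study-day clock is separate: "Day 1 is the date that the first sample to diagnose mpox was taken, regardless of when results became available". A participant who starts treatment later begins a new schedule, with a second D1 on the day treatment starts.

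Collection. Under Harms (Safety reporting), AE and SAE data go into the eCRF from the date the participant's "diagnostic sample for mpox infection was collected or the date of enrolment (whichever comes first) until D28". Data collection methods and footnote b of Table 1 also have sites record, at baseline, AEs and SAEs that arose between the diagnostic sample and consent.

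Who enrols late. Under Recruitment, from January 2023 "patients managed before the start of the study at participating sites or patients from newly activated sites were recruited retrospectively". The analysis population pools prospective and retrospective participants, and nothing in the article gives the retrospective ones a different safety window.

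**The concern.** The outcome and the data collection use different starting points. The Harms sentence names the sample date and the enrolment date as two distinct events, so enrolment cannot be read as a synonym for D1. An analyst who follows the stated outcome must discard SAEs that sites were instructed to collect, and for late enrolees must look at a period after the acute illness. An analyst who uses D1 to D28 instead departs from the outcome as written.

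Describing AEs and SAEs is a stated secondary objective, and the Harms section wants it served in treated and untreated participants alike. The treated groups are small (55 on tecovirimat, 7 on cidofovir, 2 on both), so a few omitted events could change the safety description.

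**Working it through.** The plan gives no figure to reproduce; the check is an overlap of time windows.

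**Inputs**
- Collection window: study days 1 to 28, D1 being the diagnostic sample (Participant timeline; Harms).
- Analysis window: study day E to E + 28, where E is the study day of consent (Outcomes; Statistical methods).
- Restarted schedule: if treatment starts on study day T, its D28 is study day T + 27 (Participant timeline).

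**Step 1. Days of D1 to D28 inside the analysis window.** Overlap = max(0, 28 − E + 1) = max(0, 29 − E).

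| Enrolment day E | Days covered | Days left out |
|---|---|---|
| 1 | 28 | 0 |
| 8 | 21 | 7 |
| 14 | 15 | 13 |
| 21 | 8 | 20 |
| 28 | 1 | 27 |
| 29 or later | 0 | 28 |

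**Step 2. Retrospective recruits in calendar time.** Take consent on 1 January 2023 as an illustration. A sample on 4 July 2022 gives E = 182, one on 1 October 2022 gives E = 93, and one on 4 December 2022 gives E = 29. For that consent date, any sample on or before 4 December 2022 leaves no overlap.

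**Step 3. Sensitivity to the reading.** If the 28 days are taken to run both before and after enrolment (E − 28 to E + 28), all 28 days are covered up to E = 29. Beyond that the overlap is 57 − E: 17 days at E = 40, 1 day at E = 56, none from E = 57. This reading rescues early enrolees but not someone consenting months later.

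**Step 4. Treatment started after enrolment.** Enrolled on D1 and treated from T = 10: the restarted D28 is study day 10 + 27 = 37. The enrolment window ends on study day 28 if the enrolment day counts as day 1, or on day 29 if 28 days are added to it. The part cut off is 37 − 28 = 9 days or 37 − 29 = 8 days.

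**Step 5. Window on the collection clock.** Running the outcome from the sample to D28 covers all 28 days whatever the value of E.

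**The case against.** The best defence is that enrolment in these two sentences is loose wording. The authors deliberately capture SAEs between sample and consent, which suggests that they meant to count them, and a SAP to be finalised before any analysis will set out the safety variables. No collected data are lost, and deaths, serious complications and mpox hospitalisations also enter the D14 and D28 ordinal scale, which runs on study days. This bears on how serious the point is. It does not remove the conflict, because the anchor is stated twice and differs from the collection rule in the same article.

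Other parts of the defence limit the point, and stronger readings should be resisted:
- A reader might infer that every retrospective participant contributes an empty window. The overlap with D1 to D28 is zero only for enrolment on study day 29 or later (day 57 on the two-sided reading); earlier enrolment truncates it.
- A reader might infer that nothing is collected after D28. Data collection methods lists AE and SAE details among the content of the D60 and D180 assessments, which sits uneasily with the stop at D28 under Harms. Such data would still describe a later period than D1 to D28.
- A reader might infer a biased SAE rate. The article promises only number and type; it states no rate, denominator or group comparison for SAEs.
- A reader might attach a percentage to the understatement. That would need the retrospective share and an assumption of equal SAE risk in both groups, and the article gives neither. Nor does losing 7 of 28 days mean losing a quarter of the SAEs.

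**Conclusion.** The point holds as an inconsistency between the safety outcome and SAE collection. As written, the outcome excludes collected SAEs that precede consent. It covers 21 of the 28 days D1 to D28 for enrolment on study day 8 and none for enrolment on day 29 or later. It also ends about 8 to 9 days before the restarted D28 in the example of treatment from study day 10. The direction for D1 to D28 is an undercount, concentrated in retrospective participants. Its size cannot be computed, because neither the retrospective share of the 601 nor the distribution of enrolment days is given.

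The day counts assume a forward window and the article's own definitions of enrolment and D1. The conclusion concerns counts in a descriptive secondary outcome. It does not show that a treatment comparison is biased or that data are missing.

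**What to change.** In both the Outcomes section and the safety paragraph of the statistical methods, replace the 28 days from enrolment with the collection window: from the diagnostic sample, or enrolment if earlier, to D28. State that D28 is counted from treatment start for participants whose schedule restarts, and that SAEs before treatment start are counted as untreated. Carry the same definition into the SAP.

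Reconcile the Harms section, where collection stops at D28, with Data collection methods, where SAE details are also taken at D60 and D180, and say whether later events are reported separately.

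The cost is one sentence in each of the two places. The protocol already requires the D1 to D28 data in the eCRF. The downside is that reported SAE counts may be higher. Showing retrospective participants separately would be a useful option, but the correction does not depend on it.
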